# Protocol Summary

1. **Title**

A cluster-randomized trial evaluating a complex intervention to improve mental health and well-being of employees working in hospital – the SEEGEN trial

1. **Study Sites**

3 study locations (Aalen/Ellwangen, Heidelberg, Duisburg) with varying number of participating clusters

1. **Phase**

Confirmatory phase III trial

1. **Rationale**

Hospital employees face many challenges and stress in their daily work life, which can lead to impaired health and well-being. However, evidence-based programs to improve mental health and well-being of hospital employees are rare. SEEGEN develops and tests the effectiveness of a complex intervention to improve work-related stressors in hospital employees.

1. **Objectives**

To evaluate the effect of a complex intervention on mental health and well-being of employees working in hospital.

1. **Design**

Open cluster-randomized trial with waitlist control group

1. **Study Population**

Hospital employees at different levels of hierarchy

1. **Sample Size**

Total sample size of 720 study participants (intervention and waitlist control group)

1. **Intervention**

Hospital employees can choose one of the following modules that aim to improve managing work-related challenges: For the top management a management training to raise awareness regarding the design of health-promoting work will be offered, for all other occupational groups in leadership position a management training to strengthen the relational and stress preventive leadership competence will be offered. For all those who are confronted with a dilemma situation regardless of their professional position, a dilemma competency training will be provided. Particular attention will be given to the different life phases of the employees: While one module deals with reconciling work and family life, another module covers the topic staying healthy in hospital. The effectiveness of the modules will be assessed by various questionnaires completed by the study participants (intervention and waitlist control group). In addition, employees who do not participate in the modules but wish to participate in the SEEGEN study by answering shorter questionnaires (cluster participants) are included in the trial to measure dispersal effects of the SEEGEN study.

The outbreak of the COVID-19 pandemic led to an interruption of the complex intervention and thus made changes in the study design as well as an adjustment of the questionnaires necessary. Before restarting the complex intervention, a questionnaire (including the instruments described) will be sent to the study participants (T1*). Additional questions on the COVID-19 pandemic will be included to evaluate the mental health of hospital workers also in relation to the pandemic. At the end of the complex intervention, this questionnaire is sent out again to the study participants (T2*).

1. **Primary Endpoint(s)**

The change in the total score of the Irritation scale (IRR) according to Mohr et al. (2005) from baseline (T0) to T2* (eleven months after T0) between the intervention and waitlist control group.

1. **Secondary Endpoints**

**Main secondary outcomes:**

- Change in World Health Organization Well-Being Index (WHO-5 Well Being Index, Topp et al., 2015) from T0 to T2* between the intervention and waitlist control group.
- Change in Psychosocial safety climate (PSC-12, G. B. Hall et al., 2010) from T0 to T2* between the intervention and waitlist control group.

**Further secondary outcomes:**

- Change in the total score of the IRR from T0 to 6 months after baseline (T1*) as well as the changes from T0 to T2* and T0 to T1* for both subscales between the intervention and waitlist control group.

The change in scores from T0 to T2*, as well as from T0 to T1*, between the intervention and waitlist control group of the following:

- World Health Organization Well-Being Index (WHO-5 Well-Being Index, Topp et al., 2015)
- Psychosocial safety climate (PSC-12; 12 items, G. B. Hall et al., 2010)
- Effort-Reward Imbalance Scale – Short version (ERI, 10 items, Siegrist et al., 2009)
- Work Analysis Instrument for Hospitals – Self-Report Version (2 subscales, 6 items, Glaser, 1997)
- Questionnaire on integrative leadership (FIF, 24 items) (Rowold & Poethke, 2017)
- Short version of the Occupational Self-Efficacy Scale (SOSES; 6 items, Rigotti et al., 2008)
- Top Management Evaluation Sheet (only for top management*)*
- Organizational indicators on individual/participant level (Job satisfaction, 8 items, Fischer & Lück, 2001; Employer attractiveness, 5 items, Bruhn et al., 2013, Presenteeism, 1 item, Preisendörfer, 2010; Intention to leave, 1 item, Simon et al., 2005; Recommendation, 1 item, modified version of Reichheld, 2003; Absenteeism; 1 item, modified version of Caverley et al., 2007; Work overtime; Economic situation of clinic/unit; 1 item, adapted version of A. Hall & Rohrbach-Schmidt, 2013; Job security; 1 item, Lee et al., 2004; Cooperation between occupational groups, 2 items, TAA-KH-S subscale social climate, Glaser, 1997)
- Organizational indicators on hospital/clinic level (Turnover rate, Number of applicants, Number of persons hired, Number of persons retired, Number of dismissals, Number of expiring fixed-term contracts, Absence rate, Work overtime rate, Sickness absence rate, Age distribution) requested from the participating hospitals’ accounting divisions

The change in scores from T1* to T2*, between the intervention and waitlist control group of the following:

- COVID-19 exposure and (mental) effects (concerns about COVID-19, trust in employer etc.; 12 items, five additional open questions)

The change in scores from T0 to T2*, as well as from T0 to T1*, between cluster participants (no module participation) of the following:

- IRR (Mohr et al., 2005)
- WHO-5 Well-Being Index (Topp et al., 2015)
- PSC-12 (G. B. Hall et al., 2010)
- Global Transformational Leadership (GTL; Carless et al., 2000)

The change in scores from T1* to T2*, between between cluster participants of the following:

- COVID-19 exposure and (mental) effects

In addition, the following outcomes will be collected at T2. The inclusion of these items enables to identify predictors for Work-Life-Balance:

- Personal data that provide information about the number of own children, childcare facilities and the partner's work activity (9 items),
- Trierer scale to measure Work-Life Balance (TKS-WLB, 5 items, Syrek et al., 2011) and
- The subscales “emotional demands” and “hiding emotions” of the Copenhagen Psychosocial Questionnaire (COPSOQ, 4 items Nübling, 2005).

1. **Statistical Methods**

The primary analysis will be performed according to the intention-to-treat principle comparing the change in the total score of IRR from baseline (T0) to 11 months after baseline (T2*) between the intervention group and the waitlist control group. To account for the clustering structure, an ANCOVA approach is used for analysis, including the treatment group, baseline value of the total score of the IRR at T0, hierarchy level, gender as well as the site as covariates and the respective cluster as a random effect. In case of significance, this approach is also used to hierarchically test for the secondary outcome, the change in the WHO-5 from T0 to T2*, in a confirmatory manner. Again, in case of significance the change in the PSC-12 from T0 to T2* will also be tested. All primary and secondary outcomes will also be analysed descriptively.

1. **Study Durations and Dates**

Total study duration [24 months]

Process evaluation: [28 months]

Duration of longest intervention: [10 months]

Duration of whole intervention and observation phase: [12 months]

Beginning of the preparation phase: [11/2018]

Start of recruitment: [10/2019]

End of recruitment: [03/2020]

End of observation phase: [03/2021]

Data base lock [06/2021]

End of waitlist control intervention: [04/2021]

Statistical analyses completed: [08/2021]

Study report completed: [09/2021]

# Figure 1: Flow Diagram

[figure not shown]

# Table 1: Trial schedule

|  | T0  (for intervention and wait list control group participants) | T0  (for cluster partici-pants) | T1*  (for intervention and wait list control group participants; 6 months after T0, ± 1 month) | T1*  (for cluster participants; 6 months after T0, ± 1 month) | T2*  (for intervention and wait list control group participants; (11 months after T0, ± 1 month) | T2*  (for cluster participants;11 months after T0; ± 1 month) |
| --- | --- | --- | --- | --- | --- | --- |
| Sociodemographic aspects | x | x |  |  |  |  |
| Inclusion and exclusion criteria | x | x |  |  |  |  |
|  |  |  |  |  |  |  |
| IRR | x | x | x | x | x | x |
| WHO-5 Well-Being Index | x | x | x | x | x | x |
| PSC-12 | x | x | x | x | x | x |
| ERI | x |  | x |  | x |  |
| TAA-KH S 8 | x |  | x |  | x |  |
| FIF, Modul A – transformational leadership | x |  | x |  | x |  |
| GTL |  | x |  | x |  | x |
| SOSES | x |  | x |  | x |  |
| Top Management Evaluation sheet | x |  | x |  | x |  |
| **Organizational indicators** |  |  |  |  |  |  |
| Job satisfaction | x |  | x |  | x |  |
| Employer attractiveness | x |  | x |  | x |  |
| Presenteeism | x |  | x |  | x |  |
| Intention to leave | x |  | x |  | x |  |
| Absenteeism | x |  | x |  | x |  |
| Recommendation | x |  | x |  | x |  |
| Work overtime | x |  | x |  | x |  |
| Economic situation of clinic/unit | x |  | x |  | x |  |
| Job security | x |  | x |  | x |  |
| Cooperation between occupational groups | x |  | x |  | x |  |
| Turnover | x |  | x |  | x |  |
| Absence rate | x |  | x |  | x |  |
| Work overtime rate | x |  | x |  | x |  |
| Sickness absence rate | x |  | x |  | x |  |
| Age distribution | x |  | x |  | x |  |
| **Process evaluation** |  |  |  |  |  |  |
| SEEGEN intervention fidelity scale |  |  | x |  |  |  |
| 17 items on exposure and (mental) effects caused by COVID-19 |  |  | x | x | x | x |
| 9 items on personal data (number of own children, childcare facilities and the partner's work activity) |  |  |  |  | x |  |
| Trierer Scale to measure Work-Life Balance (TKS-WLB) |  |  |  |  | x |  |
| COPSOQ |  |  |  |  | x |  |

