## Process evaluation

Furthermore, a thorough process evaluation will be part of this trial. Up to four expert interviews will be conducted with persons not involved in the study to prepare the development of the interviews guidelines. In line with the best available evidence (Moore et al., 2015), a mixed-methods approach will be used. First, focus groups (Richter et al., 1991) (about N = 8 per group) will be conducted with a subsample of participants from all study sites before and after the implementation of the intervention to identify participants’ attitudes, perceptions, and experiences regarding the intervention. Three pre-post focus groups will be held at each study site, with participants representing an adequate mix of targets groups. If new and interesting topics relevant for the process evaluation are coming up during the interviews, additional interviews via video conferences will be conducted with participants from different study sites. The interviews will be analysed using qualitative content analysis (Mayring, 2015) via MAXQDA after transcription. Second, the entire aggregated data set will be subjected to comprehensive multivariate analysis using multilevel modelling to identify mediators and moderators of effect with a focus on context (e.g. organizational indicators), intervention (e.g. fidelity), participant characteristics, process measures (e.g. self-efficacy), and satisfaction ratings. Process evaluation includes the development of a pragmatic SEEGEN fidelity scale. The fidelity scale aims to assess and monitor fidelity of the complex process of intervention implementation in SEEGEN. Development of the scale and item selection was guided by recommendations of relevant methodological literature (Breitenstein et al., 2010; Carroll et al., 2007; Feely et al., 2018; Ibrahim & Sidani, 2015). Operational fidelity as the degree to which the intervention is delivered according to the original plan was a leading feature. A consensus-based selection of the final items was performed with a systematic rating within the study group. Five specific dimensions of fidelity are addressed:

1. Exposition (dose, frequency and duration of contact to the intervention)
2. Engagement (extent to which the participants are involved in the intervention activities and capture activities during the intervention sessions)
3. Enactment/adherence (extent to which participants actively apply the skills learned during the intervention in their daily routine)

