## Duration of Trial Period(s)

Total trial duration is 12 months, consisting of a 10-month intervention phase. The different intervention modules vary in their duration: The first intervention module – Top Management Training– has a duration of one working day, the Promoting stress preventive relational leadership competence has a total duration of 3 weeks. The third intervention module – Dilemma Competency – Coping by taking responsibility – will be administered over a period of 2 months. The intervention module Reconciling Work and Family Life has a duration of one working day while Stay Healthy at Work is offered over a period of 4 weeks. Booster sessions and the 1^st^-order round tables will take place at the beginning of October 2020, the 2^nd^-order round tables will be held at the end of October, before T2*.

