# Study process

Eligible clusters will be identified in three study locations (Aalen/Ellwangen, Heidelberg, Duisburg). Interested employees in these clusters will be informed about the study and the different interventions by means of information events or by the operational health management of the respective location. Verbal and written information will be given to all employees interested in the interventions. The study staff will contact potential participants and obtain written informed consent. A choice of five modules will be offered to the study participants with the restrictions mentioned above. For participants in clusters randomized into the intervention group, the remaining modules will start within the intervention phase. For participants in clusters randomized into the waitlist control group, the five modules will begin after the intervention phase. As a possible disadvantage, the participants in the waitlist control group might feel deterred by the long waiting time of 12 months.

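### The fidelity scale is scheduled only at T1*, before the intervention restarts, so it cannot rate the modules, booster sessions and round tables delivered afterwards

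*Protocol*

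**What the plan says.** Table 1 is the current schedule: it carries the T1* and T2* columns and the COVID-19 items. For the instrument it lists as "SEEGEN intervention fidelity scale", the row begins "SEEGEN intervention fidelity scale | | | x" and the remaining cells are empty. The one mark is in the T1* column for intervention and waitlist participants.

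Section 3 (Protocol Summary) fixes the order of events after the pandemic interruption. For T1* it says: "Before restarting the complex intervention, a questionnaire (including the instruments described) will be sent to the study participants (T1". For T2* it says: "At the end of the complex intervention, this questionnaire is sent out again to the study participants (T2".

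Delivery continues between the two. Section 10 (Study process) says of intervention clusters that "the remaining modules will start within the intervention phase". Section 8.4 (Duration of Trial Period(s)) says that booster sessions and first-order "round tables will take place at the beginning of October 2020", and that second-order "round tables will be held at the end of October, before T2".

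Section 5.3 (Process evaluation) gives the scale five dimensions: exposure, engagement, enactment or adherence, perceived competence of the interventionist, and satisfaction. Its purpose is to monitor how the whole complex intervention is implemented. The same section plans multilevel models to "identify mediators and moderators of effect with a focus on context (e.g. organizational indicators), intervention (e.g. fidelity").

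**The concern.** Participants cannot rate sessions that have not yet happened. With one administration before the restart, the scale covers only what was delivered before the interruption.

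The gap falls partly on the structural arm of the programme. Section 7.6 describes the round tables as the route by which measures at the structural level are developed and put to decision-makers. The introduction states the trial's purpose as testing behavioural and organisational elements in combination. As tabulated, the scale would cover no round table and no booster session.

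The process evaluation would relate fidelity to an effect measured at T2*, with fidelity recorded before part of the exposure had occurred. After an interrupted intervention, readers will want to know how well the resumed part was delivered and taken up. The instrument built for that purpose would not tell them.

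**Working it through.** The protocol gives no figure on this point, so the check sets its statements side by side.

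**1. Order of events**

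- T1*: before the restart (section 3). The fidelity scale is marked here (Table 1).
- Remaining modules: within the intervention phase (section 10). Read with section 3, these are the modules still to be run after the interruption. That reading is an inference from the word for what is left over.
- Booster sessions and first-order round tables: beginning of October 2020 (section 8.4).
- Second-order round tables: end of October, before T2* (section 8.4).
- T2*: end of the intervention (section 3). The fidelity scale is not marked here (Table 1).

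Administrations of the scale at or after the restart: 0.

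**2. Calendar check**

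Section 3 gives recruitment from 10/2019 to 03/2020, and Table 1 puts T1* at 6 months after T0, ± 1 month. Assuming T0 falls in the recruitment period:

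- earliest nominal T1*: 10/2019 + 6 months = 04/2020
- latest nominal T1*: 03/2020 + 6 months = 09/2020

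Nominal T1* therefore precedes October 2020 for everyone. Only at the far edge of the window (03/2020 + 7 months = 10/2020) could a late recruit's T1* reach October, and section 3 would still require it to precede the restart.

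**3. What other planned data cover after T1***

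- *Exposure:* covered. Section 6.3 lists the number of sessions, overall and per module, as a process measure separate from the scale. Section 13.2 defines the per-protocol set by attendance at one or more module sessions and uses individual participation in round tables and booster sessions as a covariate. These must therefore be recorded.
- *Engagement, enactment, perceived competence, satisfaction:* no participant-level score. Section 5.3 plans three pre-post focus groups per site with about 8 people each. Over three sites that is 3 × 3 × 8 = 72 people. Even if all came from the intervention group, this is 72/360 = 20% of the planned 360. The share would be larger if fewer were enrolled, and extra interviews are possible. The data are qualitative and give no individual score for a multilevel model.

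Four of the five dimensions thus have no scheduled participant-level measurement for components delivered after T1*.

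**4. Consistency of the sections on the scale**

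- Section 3 says the T1* questionnaire is sent again at T2*; Table 1 leaves the fidelity cell at T2* blank.
- Section 5.3 says recipients complete the scale alongside the trial and gives no time point.
- Section 6.3 calls it the UPSIDES fidelity scale and refers back to section 5.3, which describes the SEEGEN scale.

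**The case against.** The strongest reply is that Table 1 may not be the whole process-evaluation schedule. Section 12.1 says process-evaluation data are collected and stored separately, and dose counts and focus groups are planned without appearing in Table 1. Section 3 also has the T1* questionnaire sent again at T2*. If the scale is part of that questionnaire, a repeat at T2* is implied. This has some force: a later administration is not excluded. But no section states one, and the only schedule that names the scale leaves T2* empty. On this argument the protocol contradicts itself, and the sections still need to be reconciled.

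A second reply is that the analysis is exploratory. That stands. Section 13.2 makes everything outside the three hierarchical tests descriptive, which limits the weight of the point but does not remove it.

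A reader might also infer three stronger things that the protocol does not support:

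- *That delivery and uptake after the restart are never measured.* Dose, attendance and booster or round-table participation are recorded, and focus groups follow implementation.
- *That later attenders would receive falsely low fidelity scores.* The scale is for recipients of the intervention. Someone not yet trained at T1* would more naturally have a missing score, and nothing in the protocol fixes a direction of bias.
- *That a particular share of participants is affected.* The protocol does not say how many modules ran before and after the interruption. Anyone who finished a module before it can rate that module validly at T1*.

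**Conclusion.** The point holds for the scale itself. As scheduled, it cannot capture participant-rated engagement, enactment, trainer competence or satisfaction for the remaining modules, the booster sessions or the round tables. All scheduled booster sessions and round tables are outside its reach; the share of module participants outside it is unknown and could not be derived.

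The consequence is missing or incomplete fidelity scores in the planned mediator and moderator models of the T0 to T2* effect. Dose and attendance can still show whether people came, so it would go too far to say that the trial cannot tell failed implementation from an ineffective programme. It would be less able to do so, because attendance says little about quality or enactment. The primary estimate, the type I error and the power are not touched.

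The conclusion assumes that Table 1 is complete for this instrument and that the order of events in section 3 was the order intended. It should be corrected because it changes what the process evaluation can conclude and is cheap to mend.

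**What to change.** 1. Mark the fidelity scale at T2* in Table 1 for the intervention group. Word it so that each person rates the modules, booster sessions and round tables actually attended.
2. Use the T2* score in the mediator and moderator models. Use the T1* score only for participants who had completed their module by then.
3. Align the Protocol Summary, Table 1, section 5.3 and section 6.3 on when the scale is given, to whom, and under what name.

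If T2* has already been sent without the scale, limit the fidelity models to participants whose module was complete by T1* and report that booster sessions and round tables were not rated.

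The cost is a few minutes of participant time in a questionnaire that is being sent anyway. Those trained early face longer recall, which is a reason to keep their T1* rating. A T2* score is also reported together with the T2* outcome, so its relation to that outcome should be read as an association.

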# Abbreviations and Definitions

CRF Case Report Form

COPSOQ Copenhagen Psychosocial Questionnaire

DBL Database Lock

ERI Effort-Reward Imbalance

FIF Fragebogen zur integrativen Führung [Questionnaire for integrative leadership]

GCP Good Clinical Practice

GTL Global Transformational Leadership

HC Health Circle

ICH International Conference on Harmonisation of Technical Requirements for Registration of Pharmaceuticals for Human Use

IEC Independent Ethics Committee

IG Intervention Group

IMBI Institute of Medical Biometry and Informatics

IRR Irritation Scale

LKP Leiter der Klinischen Prüfung

PSC Psychosocial Safety Climate

SOC Selection, Optimization and Compensation

SOSES Short version of the Occupational Self-Efficacy Scale

TAA-KH-S Tätigkeits- und Arbeitsanalyseverfahren für das Krankenhaus

TKS-WLB Trierer Scale to measure Work-Life Balance

WCG Waitlist Control Group

